### Randomisation

An independently controlled, computer generated randomisation will be implemented in REDCap [16, 17] by an externally based datamanager. The allocation will be concealed to the involved assessors. Only the project management has access to the randomisation information in REDCap and only after each patient has been randomised. The project manager informs the physiotherapist at the ward about the allocation. Afterwards, the physiotherapist informs the patient. A stratified block randomisation of severity of impairment based on Modified Rankin Scale (mRS) (< 4) and a block size of 4 with an intervention/control ratio of 1/3 will be performed. Furthermore, a stratification on the two participating neurorehabilitation units will be performed.

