### Outcomes

The primary outcome measure is MIP assessed by Power Breath [18]. This is an objective measurement used to describe the inspiratory capacity.

Secondary outcome measures include the following: the Functional Independence Measure (FIM) to assess the degree of dependency in daily activities—both total score and motor sub score [19]—and the 6-min walking test to measure endurance [20–22]. Fatigue was measured by the Fatigue Severity Scale [23, 24]. Average voice volume will be measured by recording of an a-sound with the app Voice Analyst. Phonation endurance (how long the a-sound lasts) is noted. The patient tries three times, and the average is then calculated. Expiratory function is as follows: peak expiratory flow (PEF), forced expiratory volume in 1 s (FEV1), forced vital capacity (FVC) and FEV1/FVC ratio will be assessed with Spirometry device (Vitalograph Micro 6300, Ireland). All respiratory measures are performed in sitting position. The patient tries three times. Subsequently, the best score is used for further analysis [12].

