### Test procedure

All assessments will be conducted at baseline, 3 weeks (at termination of the intervention) and 3 months after the intervention concluded. The Patient Global Impression of Change (PGIC) scale will be employed upon conclusion of the intervention [25].

Outcome assessors are blinded to the intervention. Testing takes place in a specific room at the recruitment hospital. Outcome assessors are physiotherapists trained in performing the test procedures and are not joining the treatment team at the recruiting ward. Patients will be tested by the same therapist all three times. The trial participants and intervention providers are not blinded.

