### Statistical analysis

Data will be analysed as intention-to-treat and per protocol. Between-group differences (3-month follow-up minus baseline) are compared by the *T* test. Regression analysis is conducted with adjustment for the confounders’ age and time from stroke to baseline assessment.

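### The planned MIP analysis does not adjust for baseline MIP or the two stratification factors: valid under randomisation, but a nearly free gain in precision, of unknown and possibly modest size, is passed up

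*Protocol article*

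**What the plan says.** All references are to the protocol article.

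- **Statistical analysis:** "Between-group differences (3-month follow-up minus baseline) are compared by the" t test. Then "Regression analysis is conducted with adjustment for the confounders", and the covariates named are "age and time from stroke to baseline assessment". The section does not say which of the two analyses is the main one, or whether the regression models 3-month MIP or its change.
- **Outcomes:** "The primary outcome measure is MIP assessed by Power Breath".
- **Test procedure:** "All assessments will be conducted at baseline, 3 weeks (at termination of the intervention) and 3 months after the intervention concluded". Baseline MIP is therefore planned for every patient. It also decides eligibility (Inclusion criteria).
- **Randomisation:** blocks are stratified by mRS, cut at below 4, and "a stratification on the two participating neurorehabilitation units will be performed".
- **Sample size:** 60 intervention and 20 control patients, 10% dropout, an SD assumed three times larger in the intervention arm, and a smallest relevant difference of 5 cmH2O. The section gives no absolute SD, alpha, power or correlation between baseline and follow-up.

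**The concern.** A change score is a baseline adjustment with the coefficient fixed at 1. The trial admits only patients whose MIP is below the norm, so some regression to the mean is likely and the true slope of follow-up on baseline may be below 1. Subtraction then over-corrects whatever chance difference in baseline MIP arises, and in a trial with about 20 patients in the smaller arm that difference can be appreciable. Age and time since stroke do not repair this.

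The randomisation is also stratified on two factors that the analysis then drops. If either predicts change in MIP, the balance bought by stratifying is not credited in the standard error.

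Calling the covariates confounders is loose wording for a randomised comparison. Covariates should be chosen for prognostic value and to match the design. What is at stake is precision and the match between design and analysis, not validity.

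**Working it through.** **1. The plan's own figure.** The 60/20 split cannot be reproduced, because alpha, power and absolute SDs are not given. It can be solved backwards. Completers are 0.9 × 60 = 54 and 0.9 × 20 = 18. With control SD of change s and intervention SD 3s, SE = s × √(1/18 + 9/54) = 0.471s. Assuming two-sided 5% and 80% power, 5 / (1.96 + 0.84) = 1.785, so s = 3.79 and 3s = 11.36. Assuming 90% power they are 3.27 and 9.82. One-sided 5% gives 4.27/12.80 (80%) and 3.62/10.87 (90%). The implied control SD is therefore about 3.3 to 4.3. A 3:1 split is optimal for a threefold SD ratio, so the design is consistent in itself.

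**2. Effect of adding baseline MIP.** Let k = (absolute slope of change on baseline) × (baseline SD), with the same slope in both arms.

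- Variance of the change-score difference: 3.79²/18 + 11.36²/54 = 0.798 + 2.390 = 3.188.
- Adjustment removes k² × (1/18 + 1/54) = 0.0741k².
- Estimating the slope adds back about 3%.

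Results with an assumed baseline SD of 16:

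| Slope of change on baseline | k | Ratio before estimation cost | Simulated ratio |
|---|---|---|---|
| 0 | 0 | 1.00 | 1.03 |
| -0.1 | 1.6 | (3.188 - 0.190)/3.188 = 0.94 | 0.97 |
| -0.2 | 3.2 | (3.188 - 0.759)/3.188 = 0.76 | 0.80 |

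Simulations with baseline SDs of 26 to 44 gave 1.03-1.04 with no dependence of change on baseline. They reached about 0.75 only with a favourable common slope.

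**3. If slopes differ by arm.** Simulated cases ran from 0.91 to 1.00, but a single-slope model can do worse. At 54/18 the pooled slope takes three quarters of its weight from the intervention arm. Suppose change depends on baseline only there, with slope g and baseline SD S. The baseline contribution to the variance then goes from g²S²/54 = 0.0185g²S² to g²S² × (0.25²/54 + 0.75²/18) = 0.0324g²S². At g = -0.2 and S = 16, the increase is 0.0139 × 10.24 = 0.142, or 4% of 3.188, on top of the 3%.

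**4. Size of the mis-correction.** For a one-SE baseline imbalance and a common slope, the error left in the change score is k × √(1/18 + 1/54) = 0.272k. That is 0.44 cmH2O at k = 1.6 and 0.87 at k = 3.2. Since k cannot exceed the control SD of change, the ceiling at s = 3.79 is 0.272 × 3.79 = 1.03 cmH2O, against a relevant difference of 5.

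**5. Strata.** If the strata explain an assumed share R² of the variance, power moves from an assumed 80% to Φ(2.80/√(1 - R²) - 1.96). That is about 82%, 84% and 88% at R² = 5%, 10% and 20%. The document does not say whether mRS or unit predicts change in MIP.

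**6. Standard errors in the regression.** Under the plan's SD ratio, the pooled residual variance is (53 × 9 + 17 × 1)/70 = 7.06s². It gives 7.06 × (1/54 + 1/18) = 0.523s² for the variance of the arm contrast, against a true 9/54 + 1/18 = 0.222s². The ordinary standard error is then √(0.523/0.222) = 1.53 times too large. Adding covariates to ordinary least squares does not cure this.

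**The case against.** Several stronger readings are tempting, and the document supports none of them.

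- **Baseline imbalance is left in the result.** Taking the Table 1 spreads (26 to 44) as SDs, the SE of the baseline difference at 60/20 is 0.258 × 26 = 6.7 to 0.258 × 44 = 11.4 cmH2O, above the relevant difference of 5. The change score already subtracts that difference, so only the mis-correction remains. For mRS and unit, stratified blocks of 4 already limit imbalance.
- **The comparison is biased.** It is not. Under randomisation it is unbiased, and the error in step 4 belongs to a particular draw.
- **An error of 1.3 to 2.3 cmH2O remains.** This takes a slope of 0.8 with those same SDs (0.2 × 6.7 and 0.2 × 11.4). It would force the SD of change to at least 0.2 × 26 = 5.2, above every control SD implied in step 1.
- **Adjustment cuts variance by 10 to 25%.** The formula (1 + ρ)/2 gives this for ρ from 0.8 to 0.5, but it assumes equal variances. At baseline SDs of 26 to 44, the implied SDs of change put ρ at about 0.99 in controls and 0.88-0.98 in the intervention arm. The reduction is then under 1% and about 1-6%.
- **Omitting the strata inflates false positives.** It makes the standard error conservative.

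It can also be said that a condensed article leaves model details to an analysis plan. That has some force for the dependent variable and for whether the covariate list is complete. But the article does write out a covariate list, and that list leaves out baseline MIP and the design factors. Finally, a model with many terms, an interaction and robust errors leans heavily on about 18 controls. That stands, and it argues for a small model with a small-sample correction.

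**Conclusion.** The point holds as a recommended improvement in precision and in matching the analysis to the design. The planned comparison is valid, but it fixes the baseline coefficient at 1 and ignores the stratification.

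The size is unknown. With a common slope, the variance ratio lies between about 1.03 and about 0.75-0.80. This rests on 54/18 completers, the threefold SD ratio, assumed 80% power at two-sided 5%, and assumed slopes and baseline SDs. The gain may be modest or absent, and a single-slope model can lose somewhat more than 3% if the arms' slopes differ. The gain from the strata depends on a prognostic value that the document does not give.

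The Randomisation section's intervention-to-control ratio of 1/3, read literally, reverses the Sample size section, and the two need reconciling. The smaller arm is about 20 either way, but the variance figures above assume that it is the control arm.

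**What to change.** Prespecify as the main estimate a linear model of 3-month MIP (or its change; the arm estimate is the same once baseline is included) on arm, baseline MIP, mRS stratum and unit. Age and time from stroke to baseline can stay as prognostic covariates. Use standard errors that allow unequal variances between arms, with a small-sample correction. Keep the unadjusted comparison as supportive. Adjust each continuous secondary outcome for its own baseline value.

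A centred baseline-by-arm interaction is optional. It guards against the loss in step 3, at the price of a slope estimated from about 18 controls.

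The change is to wording only and uses variables the protocol already plans to record. It should be made before the data are analysed. It costs a few degrees of freedom out of about 72 evaluable patients and, with a common slope, about 3% in variance if baseline MIP turns out not to predict change.

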### Data monitoring

The trial will be monitored by the project management, who regularly will follow-up on missing data and progress in the data collection. A formal data monitoring committee is not need in this trial due to its relative small sample size (*n* = 80) and no known harms.

There are no plans for independent auditing the trial, but the investigators will follow-up on missing data in REDCap. Furthermore, the procedures in the protocol will continuously be discussed and evaluated with both the assessors and the physiotherapists implementing the IMT.

### Study organisation

This study is organised and coordinated by the research unit at the Hammel Neurorehabilitation Centre. The participating stakeholders in this study are clinicians and researchers at the Hammel Neurorehabilitation Centre. All parties participate in the Steering Committee and are involved in discussing interim results and making the final decisions about the trial.

## Discussion

The primary purpose of this study is to assess the effect of an IMT intervention in patients with reduced MIP following stroke. A secondary purpose is to assess the effect of IMT on the degree of dependency in activities of daily living, endurance in gait, fatigue, voice volume, phonation endurance and expiratory capacity. Hereby, this study accepts the call for further research made by Xiao [9].

The study assumes that by strengthening the diaphragm muscle and the intercostal muscles, patients will gain faster respiratory recovery, which, in turn, will allow them to practice or carry out activities of daily living earlier in the course of their rehabilitation. The typical length of IMT interventions is 6–8 weeks [12, 13, 26]. In 2019, the average hospitalisation in the study setting for stroke patients was 34 days (95% CI 21–52 days). The length of the intervention was set to 21 days to ensure that the intervention could be completed during hospitalisation. The duration of the intervention was also informed by positive results from the pre-study. We argue that it is interesting to investigate whether or not a shorter intervention period is sufficient for patients to experience a positive impact on MIP and the degree of their dependency in activities of daily living, endurance in gait, fatigue, voice volume, phonation endurance and expiratory function*.* Especially, we find it valuable to investigate the effect of increasing intensity in rehabilitation as the intervention is relatively easy and inexpensive to implement and may be practiced by many patients on their own as an add-on to their rehabilitation.

A broad spectrum of patients with sensorimotor deficits following stroke is expected to be included in the study, as it does not exclude patients based on the severity of their stroke. We find it important to develop interventions that may also have an impact on the more severely injured patients.

Sham IMT was considered for the control group, but was rejected for ethical reasons, as it would be time consuming for patients to do the sham intervention, which would be unethical as these patients need to economise their resources due to fatigue.

An unpublished pre-study without a control group made in one part of the setting of this study indicated improvement in voice volume and phonation endurance not previously described as outcomes associated with IMT. Some patients in the pre-study described that these favourable outcomes enabled them to have phone conversations or longer face-to-face conversations with their relatives, giving them greater quality of life. We expect to obtain further knowledge on this previously undescribed field.

The pre-study has provided useful information about how to conduct the intervention, and the assessment points were adjusted according to what proved feasible in the pre-study.

## Trial status

Enrolment of participants starts on 01 February 2021. Recruitment, follow-up assessments and data analyses are expected to be completed by the end of December 2022. See Template (Additional file 1) and the Trials populated SPIRIT checklist (Additional file 2). Protocol version 2 (August 16, 2021)

## Data Availability

During the data collection period for this study, the researchers and the assessors have access to the REDCap database. The assessors, however, have no access to information with regard to randomisation. The REDCap database automatically informs the assessors about trial progress completion. Only scientific investigators associated with this project will have access to data. The data collected in this study will be available from the principal investigator on reasonable request.

## Abbreviations

EF: Expiratory function
FFS: Fatigue Severity Scale
FIM: Functional Independence Measure
IMT: Inspiratory muscle training
mRS: Modified Rankin Scale
MIP: Maximal inspiratory pressure
RCT: Randomised controlled trial
VV&PE: Voice volume and phonation endurance
